### Follow-up and endpoints

Patients will receive daily visits from a cardiologist during hospitalization. The results of all physical examinations will be recorded, and patients will be monitored for early manifestations signaling arrhythmia, pulmonary embolism, or coronary artery injury. Blood tests will be done to measure fasting blood sugar, complete blood count, C-reactive protein, urea and electrolytes, liver function test, creatine kinase, and cardiac troponin T. An electrocardiogram (ECG) will also be obtained. Prior to the MSC infusion process, the cardiac evaluation will be completed using echocardiography. The initial EF will be established according to the wall motion score and Simpson’s rule. After the MSCs are delivered, once stable, a beta-blocker, angiotensin-converting enzyme (ACE) inhibitor, aldosterone antagonist, aspirin, ticagrelor, statin, and glyceryl trinitrate (spray or tablets) will be prescribed for the patient to use at home. A cardiac rehabilitation program will also be completed. Subsequent visits will be at ten days after discharge and then every three months when an ECG and blood tests will be requested. Echocardiography will be done during the six-month follow-up and the final visit, facilitating the evaluation of LV systolic function.

Our primary endpoint to assess the efficacy of the intervention will be the incidence of HF. Secondary endpoints include the improvement in LV function (through calculation of LVEF) after six months and after three years alongside echocardiographic changes in the left ventricular mass, left ventricular end-diastolic volume, left ventricular end-systolic diameter, and global longitudinal strain (measured via automated formulas in standard views) indices.

Data will be entered, encoded, became secure, and stored in a local database.

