### Study participants

A total of 390 patients with a history of an anterior ST-elevation MI (STEMI) treated successfully with PPCI 3–7 days earlier will be enrolled. Patients must be below 65 years old and must have severely impaired function of the left ventricle (LV), represented by an LVEF of < 40%. The participating hospitals will be the Al-Zahra Heart, Namazee, and Faghihi hospitals of Shiraz, Iran.

The inclusion criteria are as follows:Age (years): 18 to 65Either genderFirst MI in the preceding 3 to 7 daysPost-AMI LVEF < 40%Negative pregnancy test (for women of reproductive age)Written informed consent

The exclusion criteria are as follows:A history of any prior cardiac conditions (valvular, ischemic, or congenital disorders)Regional wall motion abnormalities outside the region of the infarctionLV dysfunction due to other etiologies like non-ischemic cardiomyopathy, anthracycline use, or ethanol abuse (> 6 oz./day regularly)Poor echocardiography windowActive infection, malignancy, or autoimmune disease

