### Intervention

This study will use cGMP-certified clinical-grade human WJ-MSCs (Cell Tech Pharmed Co. Ltd., Tehran, Iran). The cells will be transferred to the hospital on the same day as the infusion and are to be suspended in normal saline (0.9%). Each batch will be analyzed and certificated by a qualified individual, ensuring that the cells comply with the product specifications. Standard operational protocols will be followed during shipment and handling.

In the intervention group, all 130 patients will receive a single intracoronary infusion of 10^7^ WJ-MSCs alongside the conventional treatment that will be provided to the same number of patients in the control group. Patients in the intervention group will be taken to the cardiac catheterization lab, where the infusion of 10^7^ WJ-MSCs will be done through the intracoronary route. A bolus heparin dose (weight-based) is to be administered to patients with an activated clotting time below 200 seconds.

For catheterization, we will insert a therapeutic 6 Fr guiding catheter into the left coronary artery. Following the infusion of nitroglycerin (200 μg) through the catheter, we will assess the left anterior descending (LAD) artery and document the TIMI flow. A 0.014-inch soft-tipped guidewire wire will be inserted into the LAD at the distal edge of the stent. After passing through an over-the-wire balloon to the stented area, the balloon will be inflated until achieving occlusion. Following the removal of the guiding wire, we will connect an infusion syringe to the infusion catheter. WJ-MSCs will be infused at a rate of 2.5 ml/min and the total sample volume would be 7.5 cc. Low-pressure inflation (2–4 bar) will be performed to achieve occlusion with the balloon catheter, with complete coronary artery occlusion being ensured ahead of cell infusion through the use of dye. After the infusion of each third of the cells, we will pause the infusion, and TIMI coronary flow will be assessed with the contrast agent before the resumption of cell infusion. Once the cells are delivered across the three portions, we will place the coronary flow wire via the microinfusion catheter. No methods were used to increase adherence for this intervention as it was a one-off treatment with no need for continued adherence.

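### End-systolic cavity size is measured by a single diameter although infarct and treatment are regional; prespecifying end-systolic volume would serve the remodelling question better at almost no cost

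*Protocol article*

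**What the plan says.** All references are to the protocol article.

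- **Follow-up and endpoints.** LVEF is a secondary endpoint, worded as "improvement in LV function (through calculation of LVEF) after six months and after three years". LV mass is listed too, and for cavity size and strain the entry reads "left ventricular end-diastolic volume, left ventricular end-systolic diameter, and global longitudinal strain". End-systolic volume is not named. On method: "The initial EF will be established according to the wall motion score and Simpson’s rule". On timing after baseline: "Echocardiography will be done during the six-month follow-up and the final visit". The EF method at those later scans is not stated.
- **Study participants.** The 390 patients are to have had an anterior STEMI with successful primary PCI, and enter within a window of 3 to 7 days. Entry requires an LVEF below 40% after a first infarction. Wall motion abnormality beyond the infarct region is an exclusion, and so is a poor echocardiographic window.
- **Intervention.** The guidewire is "inserted into the LAD at the distal edge of the stent", and the balloon is inflated in the stented area before the cells are infused.
- **Statistical analysis.** Of the echocardiographic measures, only EF is given a test.

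The article gives no reason for using a volume at one end of the cycle and a diameter at the other.

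**The concern.** A linear diameter describes the ventricle at one level only. That is a fair summary of cavity size when the ventricle changes evenly. This trial selects patients whose dysfunction is confined to an anterior infarct and treats them through the artery supplying it, so the change of interest may be uneven. If it lies largely away from the measured line, the diameter will understate it. A volume summed over the whole cavity will not.

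The Discussion presents inhibition or reversal of remodelling as the aim of regenerative treatment, and end-systolic cavity size bears directly on that. At stake is how informative one secondary endpoint is. Simpson's rule obtains EF from an end-diastolic and an end-systolic volume, so the better measure is a by-product of a reading that the article already names for baseline.

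**Working it through.** The plan states no figure that depends on this choice, so there is none to reproduce. Three checks follow.

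**1. Is end-systolic volume obtainable from what is planned?**

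EF = (EDV − ESV)/EDV, so ESV = EDV × (1 − EF).

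Take an EF gain from 35% to 40% at unchanged EDV. The 5-point size follows the presumed EF difference in the Adverse events section, read here as percentage points. The EDV values are assumed.

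| EDV (ml) | ESV at EF 35% | ESV at EF 40% | Fall |
|---|---|---|---|
| 140 | 91 | 84 | 7 ml |
| 160 | 104 | 96 | 8 ml |
| 180 | 117 | 108 | 9 ml |

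In each row the ratio is 0.60/0.65 = 0.923, a fall of 7.7%.

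So ESV can be derived if EDV and EF come from the same volumetric reading. If EF partly reflects a wall motion score, the derivation is not exact. Each EF point of disagreement moves the derived ESV by 1% of EDV, or 1.6 ml at 160 ml, against an effect of 8 ml.

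**2. If the ventricle changes evenly, what does a diameter show?**

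A linear dimension scales with the cube root of volume: 0.923^(1/3) = 0.974, a fall of 2.6%. On an assumed 40, 45 or 50 mm this is 1.05, 1.18 or 1.32 mm. This only converts units. It does not show that the diameter is less sensitive, which would need the measurement variability of both quantities, and the article gives neither.

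**3. If the change is regional, what does a diameter show?**

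Assume a cavity 8 cm long, cut into 20 discs, with basal end-systolic diameter 4.5 cm and diameter 4.5 × √(1 − 0.98x²) at fractional distance x from the base. The starting volume is 85.7 ml. Only the distal discs are shrunk.

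| Distal part that shrinks | Diameter reduction there | Fall in ESV | Change in basal diameter |
|---|---|---|---|
| one third | 5% | 1.6% | 0 |
| one third | 20% | 6.0% | 0 |
| one half | 10% | 6.0% | 0 |
| 60% | 20% | 15.7% | 0 |

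Hand check of the third row. The distal half holds (0.5 − 0.98 × 0.875/3)/(1 − 0.98/3) = 0.214/0.673 = 31.8% of the volume. A 10% smaller diameter gives 1 − 0.9² = 19% less area, and 0.318 × 0.19 = 6.0%.

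The zero in the last column is built in by placing the line at the base and the change elsewhere. The model shows that a one-level measure can miss regional change. It does not estimate how often or by how much it would do so here.

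**The case against.** Much of the case on the other side stands.

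- **The level of the diameter is not stated.** A basal line is an assumption. A reader might infer that the line crosses only segments required to be normal. The article does not support that: it excludes abnormality outside the infarct region but sets no limit on how far an anterior infarct extends, and an LVEF below 40% with the other walls normal suggests a large one. The stent's position in the LAD is not given either, so the treated segments cannot be placed relative to the line.
- **Other listed measures respond to infarct-zone change.** LVEF, end-diastolic volume and global longitudinal strain all do. A reader might infer that the plan cannot show whether an EF gain comes from a smaller end-systolic cavity. That goes too far, because ESV can be derived as in check 1 when the methods match.
- **Misreporting is speculative.** A reader might expect a null diameter result to be presented as absence of reverse remodelling. Nothing in the article gives the diameter that role.
- **The list may not be complete.** It is introduced as what the secondary endpoints include, and a journal article condenses the full protocol.
- **The fix is not entirely free.** Simpson's rule is named only for the initial EF, so volumetric tracings at follow-up are inferred.

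These points limit the size of the concern and the strength of its wording. They do not answer it. The article names the diameter as the end-systolic measure of cavity size. Wherever that line is drawn, it samples one level of a ventricle whose disease and treatment are regional. A volume derived after the fact would not be a prespecified endpoint.

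**Conclusion.** The point holds as a low-cost improvement to one secondary endpoint. A one-level end-systolic diameter can miss infarct-zone change that an end-systolic volume would register. The extent cannot be fixed from the article: in the illustrative model the missed fall in ESV runs from 1.6% to 15.7%, and this range rests on assumed dimensions, a basal line and change confined to the distal ventricle. With an even change, or an infarct reaching the measured level, the diameter would move too.

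The primary endpoint, its analysis and the sample size are untouched. The diameter is a weaker choice of measure here; it is not a contradiction or an error of fact.

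**What to change.** In Follow-up and endpoints, prespecify left ventricular end-systolic volume as the end-systolic remodelling endpoint, measured by the same Simpson method as end-diastolic volume and EF at baseline, six months and the final visit. State that Simpson's rule applies at follow-up as well as to the initial EF. Keep the end-systolic diameter as a descriptive measure.

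**Cost.** The wording of one secondary endpoint, plus a sentence on method. No extra scan, visit or patient is needed. If follow-up EF was not going to be read volumetrically, there is some added reading time.

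**Downsides.** It is a late change, since recruitment was under way when the article appeared. It should be dated, sent to the registration site as the Trial status section provides for protocol changes, and made before the database is unblinded. ESV also needs adequate apical views, but end-diastolic volume and a Simpson EF need them already, and patients with a poor window are excluded.

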### Adjudication of study measures

Before statistical analysis, adjudication of all measurements will be done by an experienced cardiology department member excluded from the research group. The adjudicator will assess the quality of each measurement and will exclude those with inadequate quality from the analysis, where they will be regarded as missing. An independent, blinded safety committee will evaluate potential major adverse cardiac events (MACEs). Once the adjudication process is complete, the finalized database will be unblinded.

### Statistical analysis

Data will be kept anonymous until analysis, which is to be performed by an independent statistician external to the research group. Continuous variables will be summarized using the mean and standard deviation, while frequencies and percentages will be given for categorical data. The analysis will follow the intention-to-treat approach. Two-sided P-values will be used and a *P*<0.05 will be considered as significant.

The primary endpoint of the study which is the incidence of heart failure will be compared between groups using Cox regression analysis.

We will consider the EF to have improved significantly if a minimum increment of 3% is achieved after six months. The EF, as the secondary outcome, will be compared between the study groups using the independent t-test.

The baseline characteristics of the two study groups will also be compared using independent sample *T*-test.

Safety will be compared between the two groups according to the occurrence of MACEs (death, recurrent AMI, ICD insertion, non-target vessel revascularization, etc.) and serious adverse events (SAEs) using COX regression analysis. These events will be followed over time with Kaplan-Meier curves, which will allow us to understand their patterns.

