### Cell-based therapy in acute myocardial infarction (AMI)

To date, BM-MNCs have been used in the majority of research on cell-based therapy following AMI. The TIME trials established that the optimal time for cell implantation following AMI is within 3–7 days [21, 22]. Fisher et a., in a meta-analysis, proved that BM-MNCs augment the left ventricular ejection fraction (LVEF) following AMI by roughly 2.72%, yielding benefits both in terms of survival and function in AMI patients younger than 55 years of age with LVEF < 37% [23].

Trials involving the use of MSCs in patients following AMI have shown promising yet controversial results. Gao and coworkers conducted the largest clinical trial in this regard with 116 patients, demonstrating that umbilical cord-derived Wharton’s jelly MSCs (WJ-MSCs) led to an almost five percent improvement in the LVEF [24]. This figure was also confirmed in a meta-analysis for those who receive the cells in the first 10 days after AMI with an improvement of around at 5.74% [25]. These are in agreement with the findings of the TAC-HFT trial, which indicated the roughly twofold effectiveness of MSCs relative to BM-MNCs [19]. Also, a head-to-head comparison of BM-MNCs with MSCs in a meta-analysis showed similar findings (BM-MNC= 3.07%, vs MSCs = 5.65%) [26].

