### Sample size

Since the primary outcome of this study is to compare the incidence of HF and considering the one-year incidence rate of 1.3% and 4% in the BAMI trial [3], it is predicted that in a 3-year period follow-up of considered for the present study, the incidence rate of this indicator will be 3.9% and 12% in intervention and control groups respectively. According to the formula $$\boldsymbol{n}=\frac{\frac{\mathbf{1}+\boldsymbol{R}}{\boldsymbol{R}}\overline{\ \boldsymbol{P}}\Big(\mathbf{1}-\overline{\boldsymbol{P}\Big)}{\left({\boldsymbol{t}}_{\boldsymbol{\alpha}, \boldsymbol{\nu}}+{\boldsymbol{t}}_{\boldsymbol{\beta} \left(\mathbf{1}\right),\boldsymbol{\nu}}\right)}^{\mathbf{2}}}{{\left(\boldsymbol{\partial}\right)}^{\mathbf{2}}}$$, and the enrolment ratio of 2:1 in case and control groups, and considering the first type error of 5% and the power of 80%, the required sample size is approximately 220 people in control and 118 people in case group***s***, which makes a total of 328 people. To increase the accuracy of sampling and the possibility of using regression models, the sample size was increased to 390 people. The sample size is approximate and the above formula is summarized. In the above formula $$\overline{P}$$, the weighted average of the values in the two groups is used, and the *t* values are equal to the 0.8 and 0.975 percentiles of the standard normal distribution and equal to 1.96 and 84. The denominator of the fraction (∂) is the difference of two amounts. R is the ratio of two groups, which is 2 here.

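### The primary Cox comparison of heart failure is described without baseline covariates; pre-specifying adjustment for baseline LVEF and age would add roughly 0 to 4 points of power and close off a later choice

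*Protocol article*

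**What the plan says.** The Statistical analysis section of the protocol article defines the primary analysis: "The primary endpoint of the study which is the incidence of heart failure will be compared between groups using Cox regression analysis". No covariate is named and none is excluded. On testing, "Two-sided P-values will be used", at the 0.05 level. The same section compares EF by independent t-test and plans t-tests of baseline characteristics between the arms.

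The Sample size section predicts that "the incidence rate of this indicator will be 3.9% and 12% in intervention and control groups respectively", with "the enrolment ratio of 2:1 in case and control groups", "considering the first type error of 5% and the power of 80" per cent. It then enlarges the trial: "To increase the accuracy of sampling and the possibility of using regression models, the sample size was increased to 390 people".

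Randomization and blinding describes permuted blocks of 6 at 2:1 and names no stratification factor. Under Study participants, age 18 to 65 and post-infarction LVEF below 40% are inclusion criteria. Follow-up and endpoints says of the echocardiography before infusion: "The initial EF will be established". Adjudication of study measures lets an adjudicator exclude measurements of inadequate quality, which then count as missing.

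**The concern.** The trial was enlarged partly so that regression models could be used, yet the one regression described for the primary endpoint carries no baseline covariate. Neither the randomisation nor the analysis, as described, deals with a chance difference in LVEF or age between the arms.

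Two things are at stake. The first is precision: with few events, a covariate that predicts heart failure takes up variation that would otherwise weaken the treatment comparison, and it does so without another patient or visit. The second is freedom of choice. Covariate modelling is left as a possibility in the Sample size section, and the Statistical analysis section plans significance tests of baseline variables. Nothing in the article would stop covariates being added or left out once those tests are known. The article does not say that this will happen; it leaves the opening.

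**Working it through.** **Inputs.** From the article: 3-year heart failure risk 3.9% (intervention) and 12% (control); total 390; 130 in the intervention arm (Intervention section); ratio 2:1; two-sided 5%; target power 80%. Controls are taken as 390 − 130 = 260, which fits 2:1, although the Intervention section also speaks of equal numbers in the control group. Assumed, because the article gives no figure: how strongly LVEF and age predict heart failure.

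**The plan's own figure.** The article states 220 + 118 as a total of 328, but these add to 338. Its formula is n = 1.5 × P̄(1 − P̄) × (1.96 + 0.84)² / 0.081².
- P̄ weighted 2:1 to control (0.093): 151 + 302, about 453 in all.
- P̄ weighted the other way (0.066): 110 + 221, about 331.

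So the stated figure does not reproduce for the actual allocation. That is a separate matter. What follows uses the planned 130 and 260. The article states no event count.

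**Expected events, full 3-year follow-up.**
- Control: 260 × 0.12 = 31.2
- Intervention: 130 × 0.039 = 5.1
- Total: 36.3, or 0.093 per patient

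The enlargement to 390 adds 390 − 338 = 52 or 390 − 328 = 62 patients, which is 52 × 0.093 = 4.8 or 62 × 0.093 = 5.8 events. That is room for few covariates.

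The Trial status section has recruitment from Jan 2021 to Nov 2022 and data to Nov 2024. With uniform accrual (assumed), 10 of 22 months of entrants reach 3 years and the rest average 2.5. Mean follow-up is (10 × 3 + 12 × 2.5)/22 = 2.7 years, and events fall to about 36.3 × 2.73/3 = 33.

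**Power, unadjusted against adjusted.** Cox simulation, 130 against 260, risks as above, complete follow-up, two standardised covariates, 6,000 runs per setting (Monte Carlo standard error about √(0.8 × 0.2/6000) = 0.5 points for each power figure):

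| Log HR per SD (HR) | Likelihood-ratio test | Wald test |
|---|---|---|
| 0.4 / 0.3 (1.49 / 1.35) | 81.8% to 82.5% | 75.4% to 77.1% |
| 0.7 / 0.4 (2.01 / 1.49) | 82.0% to 84.6% | 76.2% to 79.5% |
| 0.9 / 0.5 (2.46 / 1.65) | 82.0% to 85.9% | 76.0% to 80.7% |

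At 0.2 / 0.1 there is practically no gain. With a single covariate (Wald, about 1,000 runs), HRs of 1.25, 1.5 and 2.0 per SD give 74.9% to 75.6%, 77.7% to 78.1% and 78.0% to 80.2%. The level differs by test: the article does not say which test of the Cox coefficient will be used. As a cross-check on the unadjusted level, two-proportion power at 130/260 is 77%.

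**Chance imbalance.** The standard error of a standardised baseline difference is √(1/130 + 1/260) = 0.107, so 1.96 SE = 0.21 SD. An imbalance of 0.21 SD multiplies the HR by exp(0.21 × ln h), which is 1.05, 1.09 or 1.16 for h = 1.25, 1.5 or 2.0 per SD. Against this, the SE of the log HR is about 1/√(36.3 × 1/3 × 2/3) = 0.35.

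The chance of a false benefit finding under no effect (nominal 2.5% one-sided), given the imbalance, is approximately Φ(−1.96 + imbalance × ln h / 0.35):
- 0.21 SD favouring treatment, about 1 trial in 40: 4.3% (h = 1.5) to 6.1% (h = 2.0). Direct simulation gave 4.7% to 6.3% unadjusted and 2.7% adjusted.
- Median imbalance, 0.674 × 0.107 = 0.07 SD, favouring treatment: 3.0% to 3.5%.
- 0.21 SD against treatment: 1.4% to 0.9%.

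Averaged over randomisation, the unadjusted test keeps its nominal level.

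**The case against.** The strongest reply is that this is read from silence. The article never calls the model unadjusted, Cox regression can carry covariates, the Sample size section leaves regression models open, and a covariate list is commonly left to an analysis plan that is not shown. That stands against any claim that the plan rules adjustment out. It does not remove the point: the method as described is a two-group comparison, and adjusting it for two variables already collected is a concrete improvement. If adjustment is in fact intended, fixing it in advance matters for the same reason.

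Several stronger readings are tempting, and the documents do not support them.
- A reader might infer that an unadjusted analysis inflates type I error. It does not. The raised false-benefit rates hold only given a rare imbalance in one direction, and are offset by lower rates in the other.
- A reader might take the Introduction's meta-analysis result, "yielding benefits both in terms of survival and function in AMI patients younger than 55 years of age with LVEF < 37" per cent, as showing that LVEF and age predict heart failure. It reports in whom bone marrow mononuclear cells helped. The gain from adjustment depends on prognosis, which that result does not address.
- A reader might expect a large gain. Entry limits on LVEF and age narrow the spread of both, so strong effects per SD may be optimistic, and follow-up shorter than 3 years would reduce events.
- A reader might assume a usable baseline LVEF in every patient. The adjudicator may set measurements to missing, so a model using the adjudicated value could drop randomised patients from the intention-to-treat analysis. A poor echocardiography window is an exclusion, so few should be affected, but the fix has to allow for it.

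**Conclusion.** The point holds as a worthwhile, low-cost improvement. The primary analysis as described is valid but leaves precision unused and the choice of covariates open. The gain is roughly 0 to 4 points of power. It is near 0 if LVEF and age are weak predictors within the enrolled range, and reaches 3.9 points (likelihood-ratio) or 4.7 points (Wald) only at assumed HRs of about 2.5 and 1.65 per SD. These figures rest on the plan's rates, complete 3-year follow-up, 130 against 260 patients and assumed prognostic strengths. The benefit for imbalance concerns how credible the single realised result is, with only about 5 treated-arm events expected; it does not concern the validity of the test. The benefit that depends on no assumed strength is that a fixed model removes the option to choose covariates after the baseline comparisons.

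**What to change.** In the Statistical analysis section, before the database is unblinded, define the primary analysis as a Cox model with treatment, baseline LVEF (continuous) and age (continuous). State that the LVEF recorded at entry is used, so that no randomised patient is lost if the adjudicator later excludes a measurement. Report the unadjusted hazard ratio as supportive. State that the baseline t-tests play no part in choosing covariates, and add no further covariates: three parameters on about 36 events is sustainable.

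The cost is a few lines of text, with no added patients, visits or data. The downside is small: the hazard ratio becomes conditional on the covariates, and two more parameters are fitted.

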The patients in both control and intervention groups will also receive standard Guideline directed medical therapy for acute myocardial infarction, consisting of Aspirin, ticagrelor, rosuvastatin, valsartan, and bisoprolol. Also based on the situation eplerenone and ICD insertion would be considered.

The original design of the study included a sham procedure for the control group but the local ethical committee refused that due to its invasive nature and obliged us to omit the sham procedure from the study protocol.

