### Adverse events

Adverse events will be reported by the study’s executive committee to an independent Data and Safety and Monitoring Board (DSMB). The DSMB will have the authority to stop the trial early if patient safety is compromised or if the primary research objective is met. If the presumed 5% statistically significant difference in EF was achieved, it would be considered as reaching the primary objective of the study. A stringent statistical threshold would be used as the stopping rule. All safety issues (unanticipated SAEs, mortality, intracoronary infusion complications, severe arrhythmias, etc.) will be monitored by the DSMB, and the DSMB statistician will report the occurrence of safety issues in each study group quarterly. All deaths will be reported. Auditing would be done by DSMB on a 6-month interval and is independent of investigators.

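### EF is compared by a t-test with no baseline adjustment and no stated outcome variable, and a 3% rise without reference to controls is called significant

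*Protocol article*

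**What the plan says.** Two consecutive sentences in the Statistical analysis section of the protocol article deal with EF. The first sets a rule for improvement: "We will consider the EF to have improved significantly if a minimum increment of 3% is achieved after six months". The second names the test: "The EF, as the secondary outcome, will be compared between the study groups using the independent t-test". Neither mentions baseline EF as a covariate, and neither says whether the tested variable is follow-up EF or change from baseline. The same section says "Two-sided P-values will be used", with significance at P<0.05.

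The Follow-up and endpoints section words the endpoint as an improvement: "Secondary endpoints include the improvement in LV function (through calculation of LVEF) after six months and after three years". It also describes the baseline measurement, by echocardiography before the infusion: "The initial EF will be established according to the wall motion score" (and Simpson's rule). Baseline EF is also an entry condition under Study participants: patients "must have severely impaired function of the left ventricle (LV), represented by an LVEF of < 40" (percent).

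Two further places bear on the point. The Intervention section gives background therapy to everyone: "The patients in both control and intervention groups will also receive standard Guideline directed medical therapy for acute myocardial infarction". The Adverse events section uses another EF figure: "If the presumed 5% statistically significant difference in EF was achieved, it would be considered as reaching the primary objective of the study".

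**The concern.** Baseline EF is known for patients in both arms before treatment, and it should predict later EF. A plain two-sample t-test makes less use of that information than it could, so the estimated EF effect is less precise and more exposed to chance baseline imbalance than it need be. Because the tested variable is not named, an analyst could also choose between follow-up EF and change after seeing the data.

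The 3% sentence is a separate weakness. As worded it describes a rise over time, with no control arm and no test. Patients enter 3 to 7 days after an infarct, are selected for low EF, and are treated in both arms. Recovery and regression to the mean can therefore raise EF without cells.

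EF is a secondary endpoint, but the Adverse events section ties an EF difference to the primary objective and so to early stopping. That gives the EF analysis more weight than a secondary endpoint usually carries.

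**Working it through.** **What the article provides.** It gives no SD, correlation or power for EF, so there is no EF figure to reproduce. Its sample-size calculation concerns HF incidence and does not bear on this point. Arm sizes are taken as 130 intervention (Intervention section) and 390 − 130 = 260 control. The correlation r between baseline and follow-up EF is assumed at 0.3, 0.5 and 0.7, and the SD of EF at 6 to 12 points. The 3% and 5% are read as EF points.

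**Step 1: variance of the treatment difference.** With a common SD s at baseline and follow-up, and ignoring the single degree of freedom spent on the covariate, the variance per patient is:
- t-test on follow-up EF: s²
- t-test on change: s²(2 − 2r)
- ANCOVA: s²(1 − r²)

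The ANCOVA variance is therefore 1 − r² of the first and (1 − r²)/(2 − 2r) = (1 + r)/2 of the second.

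| r | ANCOVA / follow-up EF | reduction | ANCOVA / change | reduction |
|---|---|---|---|---|
| 0.3 | 0.91 | 9% | 0.65 | 35% |
| 0.5 | 0.75 | 25% | 0.75 | 25% |
| 0.7 | 0.51 | 49% | 0.85 | 15% |

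These ratios do not depend on arm sizes or on s. The trend with r reverses between the two readings. If the SDs differ (s0 at baseline, s1 at follow-up), the variance of change minus the ANCOVA variance is s0² + s1² − 2r·s0·s1 − s1²(1 − r²) = (s0 − r·s1)². This is never negative, so ANCOVA does not lose to change, but the gain can be smaller than in the table.

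**Step 2: power for a 3-point difference.** At SD 10 the standard error of the t-test on follow-up EF is 10·√(1/130 + 1/260) = 1.07, and two-sided 5% power is Φ(3/1.07 − 1.96), about 79.8%. Multiplying the standard error by √(1 − r²) for ANCOVA or √(2 − 2r) for change gives:

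| r | follow-up EF | change | ANCOVA |
|---|---|---|---|
| 0.3 | 79.8% | 65.6% | 83.3% |
| 0.5 | 79.8% | 79.8% | 89.7% |
| 0.7 | 79.8% | 95.0% | 97.4% |

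At r = 0.5 and other SDs, follow-up EF against ANCOVA gives 99.6% against more than 99.9% (SD 6), 93.7% against 98.1% (SD 8) and 64.3% against 76.7% (SD 12). For a 5-point difference the t-test on follow-up EF already has at least 97% power across SD 6 to 12.

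**Step 3: the 3% rule with no treatment effect.** If EF changes by mean m with SD of change c in both arms, the share of patients rising by at least 3 is 1 − Φ((3 − m)/c).
- m = 5 (assumed): 63.1%, 59.9% and 57.9% for c = 6, 8 and 10. The mean rise in an arm of 130 reaches 3 with probability 1 − Φ((3 − 5)/(c/√130)), which is 98.9% at c = 10 and higher at c = 6 and 8.
- m = 0: 30.9%, 35.4% and 38.2% of patients still meet it.

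Read as a rise over time, the rule cannot separate a treatment effect from recovery common to both arms.

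**The case against.** The best defence has four parts.

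1. Under randomisation the t-test is unbiased and its standard error already allows for chance imbalance. This stands: the loss is one of precision, not validity.

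2. A reader might infer that the t-test ignores baseline EF altogether and that adjustment could be worth nearly doubling the sample (1/0.51 = 1.96 at r = 0.7). The article does not support that as a general statement. Its wording of the endpoint as an improvement fits a test on change equally well. Baseline would then be subtracted, and the gain at r = 0.7 would be 15%, not 49%. Restriction to EF below 40% also narrows the baseline range, which may keep r low and the gain over follow-up EF modest.

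3. A reader might infer that an uncontrolled 3% rise will be reported as efficacy. The next sentence prescribes a comparison between arms. If controls rose equally, that comparison would be expected to show no difference. The 3% may have been meant as a minimum relevant effect or a responder definition. This limits the harm, but the wording still attaches significance to a rise with no comparator.

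4. Adjustment is often left to an analysis plan, and the Sample size section mentions regression models. However, the article names the t-test for EF outright, so this is a stated choice and not an omission.

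Two caveats concern the inputs. The adjudication section lets poor-quality measurements be set to missing, so a few baseline values may not survive to analysis. The Intervention section also speaks of equal numbers in the two arms, which conflicts with 130 and 260. That affects the power figures in the working but not the variance ratios.

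**Conclusion.** The point holds as a matter of precision and wording. ANCOVA improves on the planned test under either reading: the variance falls by 9% to 49% against follow-up EF or by 15% to 35% against change, for r between 0.3 and 0.7 and equal SDs. Neither r nor the SD is in the article, so these are ranges and not estimates for this trial. The practical loss is largest for a difference of about 3 points with a large SD. For 5 points, power is ample with a t-test on follow-up EF.

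The 3% sentence should not stand as a criterion of significance, because it has no control reference. The documents do not show that it replaces the between-arm test. The 3% rise and the 5% difference are two EF thresholds that the article leaves unreconciled. The change is worth making, but the planned t-test is not invalid.

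**What to change.** 1. Replace the t-test with ANCOVA of EF at six months and at the final echo, with treatment arm and baseline EF in the model. Report the adjusted between-arm difference with 95% CI. The treatment effect is then the same whether the outcome is follow-up EF or change, so the ambiguity disappears.
2. Take baseline EF from the same pre-randomisation measurement in both arms.
3. Do the same for LV mass, volume, diameter and strain where a baseline exists.
4. Stop using a 3% within-arm rise as a criterion of significance. State any EF difference regarded as relevant as a between-arm difference, and reconcile it with the 5% difference in the Adverse events section.

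The cost is a few sentences of analysis text. No new data or visits are needed, because baseline EF is already collected.
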